### Secondary outcomes

Soft tissue changes: A periodontal probe and a stent put on the reference point will be used to assess soft tissue height changes in the mesial, middle, and distal regions of the buccal area of the implant site following implant placement at the surgical visit, 3 months, and 6 months after implant placement [3, 11]. Soft tissue thickness will be assessed at the 4 and 8 mm apically of the mid-buccal gingival margin. It may be done using an 15-endodontic file [11] at 2 weeks, 3 months, and 6 months after implant placement [11]Implant failure: Any implant removed after placement due to mobility, progressive marginal bone resorption, infection, or any mechanical complication during and after the surgery that cannot be forecasted before the procedure (e.g., implant fracture) [16, 17]Prosthetic failure: Any prosthesis which fails with the implant or cannot be placed in terms of implant failure or will be replaced for any reason [16]Biological or prosthetic complications [6]Subjective patient satisfaction of the surgical results: Patient satisfaction esthetically and financially after implant placement [7] will be measured applying three questions, functionally, esthetically, and undergoing a similar treatment again during 1 year of follow-up. It will be performed by possible answers for questions 1 and 2 are “yes, absolutely = 4,” “yes, partially = 3,” “don’t know = 2,” “rather not = 1,” and “Absolutely not = 0.” For question 3, “yes = 1” or “no = 0” [18]

## Sample size

Using the PASS sample size program, the present research sample size was calculated (version 11.0). Paired sample t-test power analysis was used to estimate sample size. If the mean standard deviation of the changes in bone dimensions is 1.2mm and the difference in sizes is 1 mm on both sides, the minimum sample size is 12. The research starts with 15 samples for each group, with a 20% risk of sample dropout [3].

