### Allocation and randomization

#### Randomization

Each subject will be issued a numerical code that will be placed in a matching envelope that will be kept sealed until the procedure by external investigators. As a result, participants will be divided into two groups: group 1 (with bone graft) and group 2 (without bone graft). Using a web-based randomization service, an independent investigator will produce the randomized sequence (www.randomization.com). Balanced with a block size of 4, blocked randomization will be applied. Only after the implants have been implanted on the day of surgery will the surgeon open the sequentially numbered, sealed envelopes.

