## Statistical analysis

Cohen’s *k* statistic will be used to measure consistency in descriptive data. Frequency numbers (absolute and relative values) and metric data are examples of descriptive statistics (arithmetic mean, standard deviation, and median). The intra-class correlation coefficient will be used to assess consistency between the two examiners for continuous data, such as clinical parameters. The enumerated data will be reported as percentages and the measured data as mean standard deviation or median (quartile spacing). The impact of changes in measurement time between the two study groups at two times (baseline and follow-up) will be compared using an analysis of variance (ANOVA), with the kind of intervention as a between-subject factor. The height and thickness of bone and soft tissue will be quantitative variables. Implant failure, prosthesis failure, comorbidities, and patient satisfaction will all be stated exclusively in terms of frequency (percentage). SPSS 25.0 will be used for all statistical analyses. The significance threshold is specified as 0.05.

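### The sample size comes from a paired t-test, but the trial compares two independent groups; on the stated inputs the power is about 50–60%

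*Protocol article*

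**What the plan says.** The Sample size section of the protocol article states the method: "Paired sample t-test power analysis was used to estimate sample size". The inputs follow: "If the mean standard deviation of the changes in bone dimensions is 1.2mm" and "the difference in sizes is 1 mm on both sides". The result is "the minimum sample size is 12. The research starts with 15 samples for each group, with a 20% risk of sample dropout". Neither a target power nor the sidedness of the test is given there; the Statistical analysis section sets the significance threshold at 0.05.

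The design is parallel. Under Randomization, "participants will be divided into two groups: group 1 (with bone graft) and group 2 (without bone graft"), in balanced blocks of 4, so each patient receives one treatment. The Statistical analysis section compares baseline and follow-up between the study groups by ANOVA, "with the kind of intervention as a between-subject factor". No split-mouth or matched design is described anywhere.

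**The concern.** Each patient is measured twice, so there is pairing over time within a patient. There is no pairing between the two treatments. A paired t-test on change asks whether one group's mean change differs from zero. The trial asks whether mean change differs between grafted and ungrafted patients.

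The SD in the protocol is already that of change, so the gain from measuring each patient twice has been counted. Comparing two independent mean changes then doubles the variance, yet the number from the paired calculation was carried over as the number per group.

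At stake is how the primary result will be read. If grafting truly preserves 1 mm of buccal bone, the trial has roughly a 40–50% chance of a non-significant result. The Introduction describes disagreement over whether grafting these gaps makes a difference, and the Discussion says the data will help in choosing treatment. A non-significant result from a trial described as adequately sized could easily be taken as evidence that grafting makes no difference.

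**Working it through.** **Inputs from the protocol article**
- SD of change: σ = 1.2 mm (Sample size).
- Difference: δ = 1 mm (Sample size), so δ/σ = 1/1.2 = 0.833.
- Minimum n = 12; dropout 20%; 15 per group enrolled (Sample size).
- Significance level 0.05 (Statistical analysis).
- Allocation 1:1 (Randomization).

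**Assumptions**
- Two-sided testing. This is not stated, but the planned ANOVA is non-directional.
- 80% power as a benchmark, since no target is stated. The power figures in step 3 do not depend on it.
- δ = 1 mm is taken as the between-group difference in mean change.

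**1. Reproducing the stated 12**

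Paired (one-sample) formula, normal approximation:

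n = [σ(z₀.₉₇₅ + z₀.₈₀)/δ]² = [1.2 × (1.960 + 0.842)/1]² = 11.3, rounded up to 12.

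Dropout: 12/(1 − 0.20) = 15. This step is correct and shows that 12 was used as the number per group.

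With the noncentral t distribution, the paired test has 74.8% power at n = 12 and needs n = 14 for 80% (82.2%). A one-sided paired t-test at 0.05 has 85.5% power at n = 12. So 12 fits more than one unstated setting of the paired test.

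**2. The same inputs for two independent groups**

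n per group = 2[σ(z₀.₉₇₅ + z₀.₈₀)/δ]² = 2 × 11.3 = 22.6, rounded up to 23. With the noncentral t it is 24 (power 80.7%).

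After 20% dropout: 24/0.8 = 30 per group, 60 in total.

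**3. What the planned size delivers**

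Standard error of the difference in mean change: σ√(2/n). Noncentrality: δ/SE. Degrees of freedom: 2n − 2. CI half-width: t₀.₉₇₅ × SE.

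| | 12 per group | 15 per group |
|---|---|---|
| SE | 1.2√(2/12) = 0.490 mm | 1.2√(2/15) = 0.438 mm |
| Noncentrality | 1/0.490 = 2.04 | 1/0.438 = 2.28 |
| Degrees of freedom | 22 | 28 |
| Power, two-sided 0.05 | 49.7% | 59.6% |
| Power, one-sided 0.05 | 63.0% | 72.0% |
| Difference detectable with 80% power (two-sided) | 1.44 mm | 1.27 mm |
| Expected 95% CI half-width | 2.074 × 0.490 = 1.02 mm | 2.048 × 0.438 = 0.90 mm |

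The expected half-width is about as large as the difference the trial is meant to detect.

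**4. Sensitivity to the reading of 1.2 mm**

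If 1.2 mm were the SD of a single measurement, the SD of change would be 1.2√(2(1 − r)), where r is the baseline–follow-up correlation, which the article does not give:

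| r | SD of change | Power, 12 to 15 per group |
|---|---|---|
| 0 | 1.70 mm | 28–34% |
| 0.5 | 1.20 mm | 50–60% |
| 0.75 | 0.85 mm | 79–88% |

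**5. Sensitivity to the reading of 1 mm**

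The phrase about both sides is unclear. If it meant a total difference of 2 mm, the paired formula would give 11.3/4 = 2.8, rounded up to 3, which is nowhere near 12. The stated result therefore supports δ = 1 mm.

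**The case against.** The strongest objection concerns the size of the shortfall, not the mismatch itself. The protocol states neither sidedness nor target power, its 1 mm is not clearly a between-group difference, and its SD could be read as that of a single measurement. On that last reading, with a baseline–follow-up correlation near 0.75, power would be about 80% or better.

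Part of this stands. The 80% figure is a benchmark chosen here, and 50–60% depends on the literal reading of the inputs. But the text does call 1.2 mm an SD of changes, no correlation is given, and 1 mm with 1.2 mm reproduces 12 under the paired formula. One-sided testing would raise power only to 63–72%, and a non-directional ANOVA does not support it.

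It can also be said that change scores use the within-patient pairing. They do, but that benefit is already inside the SD of change and does not remove the doubling of variance between arms.

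Finally, the protocol nowhere commits to reading a non-significant result as no benefit. That is true; the misreading is a risk, not a stated plan. Nor does condensation into a journal article explain the problem, because the article states the test used for sizing and it conflicts with the stated design and analysis.

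**Conclusion.** The concern holds. The protocol's minimum sample size was derived for a test that does not address its between-group question, and the result was then used as the number per group.

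Taking 1.2 mm as the SD of change, 1 mm as the between-group difference and a two-sided 5% level, power is 49.7% if 12 per group are evaluable and 59.6% if all 15 are. About twice the stated minimum, 24 evaluable per group, would be needed for 80%. Only the less literal reading of the SD, combined with a high correlation that the article does not state, would bring power to about 80%. The mismatch between the sizing method and the design does not depend on any of these assumptions. This must be corrected, because the sample size statement is the basis on which the primary result will be judged.

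**What to change.** Replace the paired calculation in the Sample size section with one for two independent groups, and state the sidedness, what the SD refers to, and that 1 mm is the between-group difference in mean change. Wording could be:

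*With 12 to 15 evaluable patients per group and an SD of change of 1.2 mm, a two-sided 5% two-sample t-test has 50% to 60% power to detect a between-group difference of 1 mm in mean change. The difference detectable with 80% power is 1.44 mm with 12 per group and 1.27 mm with 15 per group.*

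In the Statistical analysis section, make the between-group difference in mean change with its 95% confidence interval the main result, and add that p > 0.05 will not be interpreted as absence of benefit from grafting.

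The cost is protocol wording and a less favourable description of what the trial can detect. No additional patients are needed for this restatement, which matters because the Trial status section reports recruitment under way, with completion expected by 6 December 2022. If the investigators instead want 80% power for 1 mm on these inputs, that means enrolling 30 per group (60 in total) instead of 30 overall.

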## Data collection and management

Only research team members are allowed to gather data. Members of the study team must keep the information confidential and use it solely for scientific purposes. The information is kept on a secure platform and on paper. Investigators are given a login and password to view the data put into the platform in order to maintain privacy. To eliminate the chance of prejudice, the independent investigator will conduct statistical analysis.

## Statistical analysis

Cohen’s *k* statistic will be used to measure consistency in descriptive data. Frequency numbers (absolute and relative values) and metric data are examples of descriptive statistics (arithmetic mean, standard deviation, and median). The intra-class correlation coefficient will be used to assess consistency between the two examiners for continuous data, such as clinical parameters. The enumerated data will be reported as percentages and the measured data as mean standard deviation or median (quartile spacing). The impact of changes in measurement time between the two study groups at two times (baseline and follow-up) will be compared using an analysis of variance (ANOVA), with the kind of intervention as a between-subject factor. The height and thickness of bone and soft tissue will be quantitative variables. Implant failure, prosthesis failure, comorbidities, and patient satisfaction will all be stated exclusively in terms of frequency (percentage). SPSS 25.0 will be used for all statistical analyses. The significance threshold is specified as 0.05.

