**Method and design:**

Thirty patients who meet the inclusion criteria and have maxillary teeth (numbers 14 to 24) are candidates for the immediate implant with immediate provisionalization. Participants will be assigned randomly to one of two groups: (1) an immediate implant with xenograft and (2) an immediate implant without bone grafting. For 3 months, the temporary prosthesis will be installed shortly before the final restoration. Following temporary prosthesis insertion and 6 months after surgery, a CBCT radiograph will be used to examine bone tissue. Soft tissue will be assessed at three points: baseline, 3 months, and 6 months following implant therapy. Patients’ satisfaction, implant failure, prosthesis failure, and complications will be assessed as secondary outcomes after 6 months.

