## Intervention

### Extraction and implant

After extraction in the fresh socket, patients in group 1 (implant with bone graft) and group 2 (implant without bone graft) will receive implants with sandblasted, large grit, and acid-etched (S.L.A) implant surfaces (Implantium, Dentium, South Korea). Using a periotome and forceps, the target tooth is extracted atraumatically with a maximal effort to maintain the buccal plate without flap reflection.

In both groups, implants will be placed 3 mm measured with a millimeter-sized periodontal probe apically to the buccogingival edge of adjacent teeth. The gap width between the immediate implant surface and buccal bone will be measured after implant placement by a periodontal probe to ensure a space of more than 2 mm. Patients with a gap of <2 mm (healed spontaneously without any grafting procedure) will be excluded from the study [5]. After placing the implants, all participants will be divided into two groups: group 1 (implant with bone graft) and group 2 (implant without bone graft).

In patients allocated to group 1, the tooth socket area will be filled with xenograft (SigmaGraft, Fullerton, CA, USA) next to the implant surface after implant insertion. Group 2 will receive an immediate implant that does not need any bone graft material [6]. All surgical operations will be performed by [name]. [name], Oral and Maxillofacial Surgeon.

Prophylactic antibiotics consist of 2 g of oral amoxicillin capsules or 600 mg of oral clindamycin capsules given 1 h before surgery. With the flapless tooth extraction procedure, anesthesia including lidocaine and epinephrine 1/80,000 is injected into the tooth extraction region as infiltration and site preparation [3, 11].

All patients will get the healing abutment for about 2 weeks, once the fixture is installed. Antibiotics (amoxicillin 500mg/clindamycin 300mg) and analgesic (ibuprofen 400mg) will be used to relieve discomfort following implant surgery. The patient will be given chlorhexidine gluconate 0.12% oral rinse (every 12 h for 7 days) after-surgery instructions [3, 11].

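### Soft tissue measured at three visits is committed to a two-time, unadjusted ANOVA, which leaves the tested visit open and information collected before allocation unused

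*Protocol article*

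**What the plan says.** The Statistical analysis section of the protocol article names one between-group model: changes "between the two study groups at two times (baseline and follow-up) will be compared using an analysis of variance (ANOVA". Treatment group enters this model as its one named factor, and no covariate is listed. The same section gives the scope: "The height and thickness of bone and soft tissue will be quantitative variables". The threshold is 0.05, with sidedness not stated.

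The schedule differs by outcome.
- **Soft tissue overall (Abstract):** "Soft tissue will be assessed at three points: baseline, 3 months, and 6 months following implant therapy".
- **Soft-tissue height (Secondary outcomes):** read "following implant placement at the surgical visit, 3 months, and 6 months after implant placement".
- **Soft-tissue thickness (Secondary outcomes):** read at 2 weeks, 3 months and 6 months.
- **Bone (Primary outcome):** two CBCTs, one once the temporary prosthesis is in place and one at 6 months.

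On what is known before allocation, the Extraction and implant section says "The gap width between the immediate implant surface and buccal bone will be measured after implant placement by a periodontal probe". Patients with too small a gap are excluded and the rest are then divided into groups. The Randomization section has the surgeon open the envelope only after the implant is in.

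**The concern.** Two times fit the two CBCTs but not three soft-tissue visits. As written, the analyst can take 3 or 6 months as the follow-up after seeing both. The starting point also shifts: the day of surgery for height, but 2 weeks after surgery, and so after allocation, for thickness.

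The second issue is precision. A two-time ANOVA with group as its only between-subject factor adjusts for nothing. In a trial of 15 per group, a covariate measured before the envelope is opened is one of the few ways to gain precision while recruitment is already running.

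**Working it through.** **1. What the two-time ANOVA tests.** With two groups and two times, the group-by-time test is identical to a two-sample t-test on each patient's change.

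**2. Soft-tissue height: adjustment against change score.** Let the variance be sigma² at both times and the correlation rho. The documents give neither, so equal variance is assumed and rho is shown over a range.
- Variance of change: 2·sigma²·(1 − rho)
- Residual variance after adjusting for the first reading: sigma²·(1 − rho²)
- Ratio: (1 − rho²) / [2(1 − rho)] = (1 + rho)/2

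| rho | ratio |
|---|---|
| 0.3 | 0.65 |
| 0.5 | 0.75 |
| 0.7 | 0.85 |
| 0.9 | 0.95 |

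This applies to height only. The first thickness reading and the first CBCT come after allocation, so neither is a pre-treatment baseline.

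**3. What the 3-month visit adds.** With complete data it adds no precision to a 6-month contrast. If the target were the average of 3 and 6 months, then with all pairs of visits equally correlated the change-score variance would be [(1 + rho)/2 + 1 − 2·rho] / [2(1 − rho)] = 0.75 of the single-visit value, whatever rho is. It can also help when 6-month values are missing.

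**4. Bone: the plan's own figure first.** Inputs from the Sample size section: SD of changes 1.2 mm, difference 1 mm, paired t-test. Assumed: two-sided 0.05 and 80% power, since no power is stated. Then n = [(1.960 + 0.842) × 1.2 / 1]² = 11.3, so 12. With 20% dropout, 12/0.8 = 15. The stated figures reproduce, as a within-patient calculation.

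**5. Bone: the comparison actually planned.** Two-sample power comes from the noncentral t with noncentrality 1 / [SD × √(2/n)].
- 12 per group: 1 / (1.2 × √(2/12)) = 2.04 on 22 df, power 0.497
- 15 per group: 1 / (1.2 × √(2/15)) = 2.28 on 28 df, power 0.596

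Adding one covariate that correlates R with change gives SD = 1.2 × √(1 − R²) and costs one df. R is not in the documents.

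| R | SD (mm) | power, 12 per group | power, 15 per group |
|---|---|---|---|
| 0 | 1.200 | 0.495 | 0.595 |
| 0.3 | 1.145 | 0.533 | 0.636 |
| 0.5 | 1.039 | 0.613 | 0.719 |
| 0.7 | 0.857 | 0.778 | 0.869 |

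**6. Why the bone outcome should stay a change.** The 1.2 mm is an SD of changes. With equal variances, the SD of a 6-month value is 1.2 / √[2(1 − rho)], which is 1.2 only at rho = 0.5. At rho = 0.7 it is 1.2/√0.6 = 1.549 mm. With one covariate at R = 0.3–0.5, power is then 0.353–0.414 (12 per group) or 0.431–0.503 (15 per group), below the unadjusted change score. At rho = 0.3 the SD is 1.014 mm and power rises to 0.675–0.758 or 0.779–0.852. The result turns on a correlation that the documents do not give.

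**The case against.** The primary outcome has exactly two CBCTs, so for bone the two-time model fits. Unadjusted ANOVA is a valid comparison in a randomized trial, and a journal article commonly leaves covariate lists to the full protocol or analysis plan. Multiple imputation, planned in the Missing data section, can already use 3-month values. All of this stands. The absence of covariates is therefore not an error, and adjustment is a recommendation.

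Three stronger readings are tempting, and the documents do not support them.
- **That ignoring the 3-month visit wastes precision throughout.** There is no 3-month CBCT, and with complete data the visit does nothing for a 6-month soft-tissue contrast.
- **That every starting value is known before the envelope is opened.** The first CBCT and the first thickness reading follow allocation. The height reading is placed after implant placement at the surgical visit, but so is the envelope, and no section gives their order.
- **That bone should be analysed as an adjusted 6-month value.** This could lower power, as shown above, and it departs from the stated objective of dimensional change.

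What survives the objection is the mismatch between the schedule and the model. The article commits soft tissue to two times, measures it at three, and does not say which follow-up is tested.

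**Conclusion.** The point holds in a limited form. For soft tissue, the Statistical analysis and Secondary outcomes sections do not agree, and the tested visit is open. This concerns secondary outcomes only.

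The precision gain is real but conditional. For height it is a variance reduction of 35% at rho = 0.3, shrinking to 5% at rho = 0.9, assuming equal variances and a reading taken before allocation. For bone it is roughly 0.04 to 0.12 in power over R = 0.3–0.5, assuming the gap does predict change; if it does not, about 0.002 is lost.

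Adjustment does not repair the sample size, which rests on a paired test: "Paired sample t-test power analysis was used to estimate sample size". The covariate would need R of about 0.7 to bring 12 per group near 80% (0.778).

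**What to change.** 1. **Soft-tissue height:** name 6 months as the tested visit. Use ANCOVA, or a mixed model on the 3- and 6-month values, with the surgical-visit reading as covariate. First state that this reading is taken before the envelope is opened. If it is not, do not use it as a baseline covariate.
2. **Soft-tissue thickness:** name 6 months as the tested visit, and do not treat the 2-week reading as a pre-treatment baseline.
3. **Bone:** keep the change between the two CBCTs as the outcome and add the probed gap width as a covariate. Do not replace change with the 6-month value, and do not adjust for the first CBCT, which follows grafting.

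The cost is one degree of freedom per covariate and a change of analysis wording. The gap and height readings are already scheduled, and the planned software fits these models. The only possible change in conduct is to fix when the height reading is taken relative to the envelope. The paired-test sample size needs its own correction.
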